### Sample size

2.8

The sample size is calculated according to the main evaluation index ΔIMR at 12-month follow-up. Based on previous study, the level of ΔIMR is hypothesized to be 15.0 ± 6.0 and 10.0 ± 4.0 in study group and control group, respectively. When the calculation is performed using 90% power, and a 5% significance level (one-sided test), random distribution ratio is 1:1, the minimum number of members in each group is 25. Considering a drop-out rate of 20%, the needed sample size is approximately 32 participants for each group. Therefore, a total of 64 participants are needed for the present study.

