### Hypothesis

2.2

This study hypothesizes that for SCAD patients with normal FFR and CMVD, the addition of STDP based on the conventional drug treatment in the study group can significantly improve the coronary microvascular function compared with the control group (the key index is IMR).

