#### Primary and secondary endpoints

2.7.1

The primary endpoint is the change of Index of Microcirculatory Resistance (ΔIMR) at 12-month follow-up. The secondary endpoints are major adverse cardiovascular events (MACE, including cardiac death, myocardial infarction, ischemic stroke, unstable angina requiring hospitalization, coronary revascularization) at 12-month follow-up; the change in corrected TIMI frame count (ΔCTFC) after 1-year follow-up; the change in coronary flow reserve (ΔCFR) at 1-year follow-up.

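### The primary comparison is sized on an unexplained one-sided 5% test, although on the stated inputs a two-sided 5% test has about 92% power within the same 64 participants

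*Protocol article*

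**What the plan says.** The hypothesis in section 2.2 is superiority: adding STDP "can significantly improve the coronary microvascular function compared with the control group". Section 2.7.1 sets the endpoint: "The primary endpoint is the change of Index of Microcirculatory Resistance (ΔIMR) at 12-month follow-up".

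Section 2.8 gives the planning inputs. The assumed values are "the level of ΔIMR is hypothesized to be 15.0 ± 6.0 and 10.0 ± 4.0 in study group and control group, respectively". The calculation uses "When the calculation is performed using 90% power" and "a 5% significance level (one-sided test", and "random distribution ratio is 1:1". The result is that "the minimum number of members in each group is 25". After allowing for attrition, "Considering a drop-out rate of 20%, the needed sample size is approximately 32 participants for each group", so 64 in total.

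Sections 2.9.2 and 2.9.3 name the between-group tests (t test, or Wilcoxon rank sum for non-normal data) but attach no level and no sidedness. Section 2.8 is therefore the only place in the article where an error rate for the primary comparison appears, and it is given there without a reason.

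**The concern.** In a superiority comparison the error that matters most is declaring the treatment effective when it is not. A two-sided 5% test, or equally a one-sided 2.5% test, holds that error at 2.5%. A one-sided 5% test allows 5%, exactly twice as much. A favourable result with a two-sided p of 0.09, for example, would then count as a success.

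The article gives no argument for the lenient level. Its Introduction says that no clinical study has yet confirmed an effect of STDP on microvascular function in CAD, so the direction of the effect is not presented as clinically established. What is at stake is how convincing a positive result would be. The practical question is whether the stricter level would need more participants than planned.

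**Working it through.** **Inputs, all from section 2.8.** Mean ΔIMR 15.0 and 10.0, so the difference is δ = 5.0; SDs 6.0 and 4.0, so the variances sum to 36 + 16 = 52; power 90%; one-sided α = 0.05; allocation 1:1; drop-out 20%. Normal quantiles: 1.645 (one-sided 5%), 1.960 (two-sided 5%), 1.282 (90% power).

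**1. The plan's own figure.** With n per group = (σ₁² + σ₂²)(z_α + z_β)² / δ²:

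- One-sided 5%: 52 × (1.645 + 1.282)² / 25 = 17.8, so 18 per group. With the noncentral t (equal-variance or Welch) it is 19.
- The printed figure is 25, so it is not reproduced from the stated inputs.
- With an SD of 6 in both groups the variances sum to 72, and 72 × (1.645 + 1.282)² / 25 = 24.7, so 25. This matches the printed figure exactly. The article does not say that this SD was used.

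The drop-out step does reproduce: 25 / 0.8 = 31.25, so 32 per group and 64 in total.

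**2. Size needed at two-sided 5% on the stated SDs.** 52 × (1.960 + 1.282)² / 25 = 21.9, so 22 per group by the normal formula; 23 by the t test and 24 by Welch. Taking the largest, 24 / 0.8 = 30 per group, or 60 in total, which is within 64.

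**3. Power at the planned size.** With 25 evaluable per group the standard error is √(52/25) = 1.442 and δ/SE = 3.467. By the normal approximation:

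- one-sided 5%: Φ(3.467 − 1.645) = 96.6%
- two-sided 5%: Φ(3.467 − 1.960) = 93.4%

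The noncentral t gives slightly lower values (Welch for 6.0/4.0, equal-variance for 6.0/6.0):

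| SDs | Evaluable per group | One-sided 5% | Two-sided 5% |
|---|---|---|---|
| 6.0 / 4.0 (as stated) | 25 | 96.1% | 92.3% |
| 6.0 / 4.0 (as stated) | 32 | 98.7% | 97.1% |
| 6.0 / 6.0 (matches the printed 25) | 25 | 89.6% | 82.3% |
| 6.0 / 6.0 (matches the printed 25) | 32 | 95.1% | 90.7% |

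**4. Error rate.** In the favourable direction it is 5% for one-sided 5%, against 5% / 2 = 2.5% for two-sided 5%: a ratio of 2.

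**The case against.** Five objections deserve an answer.

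- **Decision rule.** The one-sided level appears only as an input to the sample size. A reader might infer that trial success is fixed at one-sided 5% and that a worsening of IMR could never be declared. The article does not say either. The analysis sections give no level, and the full protocol or analysis plan, which are not shown, may set a different one. This stands, so the error-rate statement is conditional on that level being used for the primary test.
- **Convention.** The hypothesis is directional, the one-sided level is disclosed, and this is a small single-centre trial with a physiological endpoint. One-sided 5% is lenient, but it is neither an arithmetical error nor a contradiction. This also stands. What remains is that no justification is given.
- **Sign of ΔIMR.** A reader might infer that the direction of the test is undefined, because improvement is a fall in IMR while the planned changes are positive. The direction can be worked out: section 2.3 requires IMR of at least 25, section 2.2 predicts improvement with STDP, and section 2.8 gives the study group the larger value. ΔIMR is evidently the size of the reduction. Writing that down is a clarification of wording only.
- **Harm.** A one-sided efficacy test does not mean that harm is ruled out. MACE and adverse events are compared separately (sections 2.9.3 and 2.9.4), with no one-sidedness stated.
- **Cost.** It is tempting to say that the one-sided level buys nothing. That holds only under SDs of 6.0 and 4.0. If the calculation really used 6 in both groups, the one-sided level is what brings 25 per group to about 90%. Even on the stated SDs, Welch needs 24 of the planned 25, a margin of one participant per group. This is the strongest objection, and the restated power has to report it.

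**Conclusion.** The point holds in a limited form. The primary superiority comparison is sized at one-sided 5% without a reason, and nothing else in the article sets a level. If that level is applied to the primary test, the chance of a false efficacy claim is 5% rather than 2.5%.

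On the stated difference of 5 and SDs of 6.0 and 4.0, the stricter two-sided 5% test keeps about 92% power with 25 evaluable per group and needs no additional participants. That conclusion depends on the stated SDs and on the 20% drop-out. The printed 25 per group casts some doubt on the SDs, since it corresponds to 6 in both groups; there, two-sided power would be about 82% at 25 per group and about 91% only if all 32 per group are evaluable. The case for the stricter level is the same under either SD. What changes is the power that can be claimed for it.

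**What to change.** In section 2.8, and wherever the primary analysis is specified:

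1. State a two-sided 5% level with a 95% confidence interval for the between-group difference in ΔIMR, or equivalently one-sided 2.5%. If one-sided 5% is kept, give the reason.
2. Confirm which SDs underlie the 25 per group. Keep 64 participants and restate power as about 92% at 25 evaluable per group under SDs 6.0 and 4.0. Report beside it the 82% (25 per group) and 91% (32 per group) that apply if the SD is 6 in both groups.
3. Define ΔIMR as baseline minus 12-month IMR, so that a positive value means improvement.

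The cost is a few sentences. Under the stated SDs, power falls from about 96% to about 92%, still above the 90% target, with no extra recruitment. If an SD of 6 in both groups is confirmed, the sponsor has to choose between accepting about 82% at 25 per group and enlarging the trial. The normal formula then gives 72 × (1.960 + 1.282)² / 25 = 30.3, so 31 evaluable per group; 31 / 0.8 = 38.75, so 39 per group and 78 in total.

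### Sample size: the printed inputs require 18 or 19 per group, not 25; the mismatch is conservative, and one sentence needs correcting

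*Protocol article*

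**What the plan says.** Section 2.8 (Sample size) of the protocol article bases the calculation on the 12-month ΔIMR. Its assumption is that "the level of ΔIMR is hypothesized to be 15.0 ± 6.0 and 10.0 ± 4.0 in study group and control group, respectively". It sets 90% power, a one-sided 5% level and equal allocation ("random distribution ratio is 1:1"), and concludes that "the minimum number of members in each group is 25". A 20% drop-out allowance then raises this to 32 per group, 64 in all. The paragraph does not say how the two unequal SDs entered the calculation. Section 2.9.3 carries the between-group method over from section 2.9.2, which is a two-sample t test for normally distributed data.

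**The concern.** The article prints every input that a two-mean calculation needs, so the result can be checked directly. It does not follow from them. A figure described as a minimum is 6 or 7 per group larger than the inputs require, which is more than rounding or the choice between a z and a t calculation can explain.

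What is at stake is the account of the design. The total of 64 rests on this step, and the calculation will be cited again when the results are reported. As written, a reader cannot tell whether the design assumes a control SD of 4.0 or 6.0, or whether 25 evaluable patients per group are meant to give 90% power or more.

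**Working it through.** **Inputs, all from section 2.8:** difference 15.0 − 10.0 = 5.0; SDs 6.0 (study) and 4.0 (control); one-sided α = 0.05, so z = 1.645; power 90%, so z = 1.2816; allocation 1:1; drop-out 20%.

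**Formula (normal approximation), per group:**

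n = (z_α + z_β)² × (SD₁² + SD₂²) / difference²

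with (1.645 + 1.2816)² = 8.564.

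**Step 1. Reproducing the plan's figure.** With SD 6.0 in both groups: 8.564 × (36 + 36) / 25 = 24.66, rounded up to 25. This matches the stated figure. A t-test calculation with the same SDs needs 26.

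**Step 2. The inputs as printed.** With SDs 6.0 and 4.0: 8.564 × (36 + 16) / 25 = 17.81, rounded up to 18. Using the noncentral t distribution, both the pooled and the Welch t test need 19 (Welch power is 89.0% at 18 and 90.5% at 19). The stated 25 therefore exceeds the derived figure by 6 or 7 per group: 25/19 = 1.32 and 25/18 = 1.39, or 32% to 39% more.

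**Step 3. Other ways to reach 25.** Averaging the two SDs to 5.0, with the other inputs unchanged, gives 18 by z or by t. Keeping both SDs but making the test two-sided gives 22 (z), 23 (pooled t) or 24 (Welch), which is close but not 25 and contradicts the one-sided level in the text. Among the variants tried that keep the stated difference, one-sided 5% level and 90% power, only the common SD of 6.0 gives 25.

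**Step 4. Power at 25 evaluable per group, one-sided 5%:**

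| SDs (study/control) | Normal approximation | t test |
|---|---|---|
| 6.0 / 4.0 | 96.6% | 96.1% (Welch) |
| 6.0 / 6.0 | 90.3% | 89.6% |

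For the normal approximation, power = Φ(5 / √((SD₁² + SD₂²)/25) − 1.645). With 6.0/4.0 this is Φ(3.467 − 1.645) = 96.6%; with 6.0/6.0 it is Φ(2.946 − 1.645) = 90.3%.

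**Step 5. Drop-out.** 25 / (1 − 0.20) = 31.25, rounded up to 32 per group and 64 in total. This step is correct, so the mismatch lies entirely in the 25. Carrying 18 or 19 through the same step would give 23 or 24 per group, 46 to 48 in total.

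**The case against.** The strongest reply is that 25 has an ordinary explanation. Taking the larger of two SDs as a common value is a cautious simplification, and with the article's own difference, level, power and allocation it leads exactly to 25, then 32, then 64. The article is also a condensed account; the full protocol is not shown and may give the method. Much of this stands. The number 25 is not shown to be a wrong choice, and the absence of a formula or software name is not a fault in an article of this kind. What does not stand is the idea that nothing needs correcting: the article printed a control SD of 4.0 beside a result that does not use it, and that conflict is within the text itself.

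Two stronger readings are tempting, and the documents support neither.

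- **That the trial is underpowered.** A reader might infer this from a power statement that does not reproduce. The error runs the other way. The 90% target is exceeded with the printed SDs and met to rounding with 6.0 in both groups. The only shortfall is 0.4 percentage points, if the common SD is combined with a t test (26 needed instead of 25).
- **That the choice of SD decides whether a two-sided test is adequately powered.** At 25 per group, two-sided 5% power is 92.3% with SDs 6.0/4.0 and 82.3% with 6.0/6.0. But section 2.8 sizes the trial on a one-sided test, and no section states a two-sided primary test. Whether a one-sided 5% level is suitable is a separate question and lends no weight to this one.

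**Conclusion.** The point holds as an internal inconsistency. The printed inputs require 18 per group (19 by t test), the article states 25, and 25 corresponds to a control SD of 6.0 instead of the printed 4.0. That a common SD of 6.0 was actually used is an inference from the exact match; the text does not state it.

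The direction is conservative. At 25 evaluable per group and one-sided 5%, power is about 96% or about 90%, depending on which control SD was meant. Both figures assume a true difference of 5.0, roughly normal ΔIMR, and drop-out no worse than the planned 20%. The number to recruit does not change. Severity: minor correction of a stated figure.

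**What to change.** Keep 25 evaluable per group and 64 in total. Check the original calculation to see which SDs were entered, then correct section 2.8 in one of two ways:

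- If 6.0 was used for both groups, say so, and leave the power at about 90% at one-sided 5%.
- If 6.0 and 4.0 are the intended assumptions, keep them and restate the power at 25 per group as about 96% at one-sided 5%, no longer calling 25 the minimum for 90%.

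The cost is rewording one paragraph. No patients are added, and the endpoint, allocation, drop-out allowance and analysis are untouched.

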### Statistical analyses

2.9

#### Descriptive analysis

2.9.1

Our descriptive statistics include that the count data is described by frequency and constituent ratio and the measurement data is described by mean, SDs, maximum value, minimum value, medians, 25^th^, and 75th percentiles.

#### Baseline demographic analysis

2.9.2

Continuous correction χ^2^ test is used for comparison between count data groups. When the theoretical frequency of more than 25% of cells is <5, Fisher's exact probability method is used; comparison between groups of normally distributed measurement data uses group *t* test; for non-normally distributed measurement data, Wilcoxon rank sum test is used for comparison between groups.

#### Efficacy analysis

2.9.3

Continuous correction χ^2^ test is used for comparison of MACE count treatment groups, paired *t* test is used for comparison of normal distribution measurement data groups; Wilcoxon sign rank is used for comparison of non-normal distribution measurement data groups (Wilcoxon Sign Rank) Test: The method of comparison between groups is the same as the baseline analysis.

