### Participant

2.3

We will enroll patients aged 18 to 80 years and the major clinical inclusion and exclusion criteria are listed in Table 2. In addition, for patients who meet clinical criteria, coronary angiography will be further performed. The inclusion criteria for the lesions are as follows: Coronary angiography shows diameter stenosis ≥50% in at least one of the three main coronary arteries with FFR ≥ 0.80. No need for revascularization (including balloon inflation, stent implantation, coronary artery bypass grafting, etc), IMR ≥ 25. At the same time, the following lesions need to be excluded:

Thrombotic lesions;Coronary spasm without significant stenosis;Left main disease with a diameter stenosis rate of ≥50%;Type C-F dissection of coronary artery.

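### The between-arm test of ΔIMR is valid but ignores baseline IMR and lets the data choose between a t test and a rank test; one pre-specified ANCOVA would be a free improvement

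*Protocol article*

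**What the plan says.** The endpoint section states: "The primary endpoint is the change of Index of Microcirculatory Resistance (ΔIMR) at 12-month follow-up". The Efficacy analysis section (2.9.3) lists paired t and signed-rank tests, which can only sensibly be before-after tests within an arm. For the comparison between arms it adds: "The method of comparison between groups is the same as the baseline analysis".

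The baseline section (2.9.2) gives that rule. For the normal case, "comparison between groups of normally distributed measurement data uses group" *t* test; otherwise, "for non-normally distributed measurement data, Wilcoxon rank sum test is used for comparison between groups". Neither section names a covariate, a criterion for normality or a time at which normality is judged.

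Two other sections matter. The lesion criteria in section 2.3 include "No need for revascularization (including balloon inflation, stent implantation, coronary artery bypass grafting, etc), IMR ≥ 25", so baseline IMR is known for everyone and everyone is selected for a high value. Section 2.5 describes simple, unstratified 1:1 randomisation.

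**The concern.** A change score removes baseline differences only if 12-month IMR rises one for one with baseline IMR. If the slope is lower, patients who start high tend to fall more in either arm. That is to be expected where entry requires a high reading. An arm that by chance starts higher then shows a larger ΔIMR without any drug effect. Nothing in the design balances baseline IMR, and the planned test does not adjust for it.

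The normality switch is a separate matter. A t test addresses a difference in means and a rank-sum test a shift in ranks. Without a stated criterion, the test and the quantity estimated for the primary endpoint are both settled after the data are in.

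**Working it through.** **The plan's own figure.** The sample-size section assumes that "the level of ΔIMR is hypothesized to be 15.0 ± 6.0 and 10.0 ± 4.0 in study group and control group, respectively", with 90% power and one-sided 5%. With the larger SD in both arms, n = 2(1.645 + 1.282)² × 6² / 5² = 24.7, so 25 per arm. Then 25/0.8 = 31.25, so 32 per arm and 64 in total. The article's figures reproduce. With both stated SDs (mean variance (36 + 16)/2 = 26), n would be 18.

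**Gain from adjustment.** The article gives neither the SD of baseline IMR nor its correlation r with 12-month IMR, so both are assumed. Take an underlying IMR with mean m and SD s, equal at both times, and entry cut at 25. Let s_b be the baseline SD after the cut. The cut leaves the slope of 12-month on baseline IMR at r. Then:

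- Var(ΔIMR) = (1 − r)² s_b² + s²(1 − r²).
- Residual variance after adjustment = s²(1 − r²).
- Variance ratio, ANCOVA to change score, at 25 per arm ≈ [s²(1 − r²) / Var(ΔIMR)] × (1 + 1/46). The last factor is the cost of estimating the slope.
- Baseline imbalance of one standard error = s_b × √(2/25). The part that enters the ΔIMR contrast is (1 − r) times this.

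For m = 25 the cut leaves a half-normal, so s_b = 0.603 s. For m = 35 and s = 6, s_b = 5.42.

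| m, s | r | s_b | SD of ΔIMR | Variance ratio | Imbalance passed on (IMR units) |
|---|---|---|---|---|---|
| 25, 10 | 0.81 | 6.03 | 5.97 | 0.98 | 0.32 |
| 25, 10 | 0.92 | 6.03 | 3.95 | 1.01 | 0.14 |
| 25, 6 | 0.5 | 3.62 | 5.50 | 0.91 | 0.51 |
| 25, 6 | 0.7 | 3.62 | 4.42 | 0.96 | 0.31 |
| 35, 6 | 0.5 | 5.42 | 5.86 | 0.80 | 0.77 |
| 35, 6 | 0.7 | 5.42 | 4.58 | 0.89 | 0.46 |

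Worked row (25, 6, r = 0.5): s²(1 − r²) = 27; (0.5)² × 3.62² = 3.27; SD = √30.27 = 5.50; ratio = 27/30.27 × 1.022 = 0.91; imbalance = 3.62 × 0.283 × 0.5 = 0.51. Simulation with 20,000 replicates agrees with every ratio to within 0.01.

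All six rows give a ΔIMR SD of about 4 to 6, as the article assumes. The variance falls by 0 to 20%. A one-standard-error imbalance moves the contrast by 0.14 to 0.77 units, or 3 to 15% of the planned 5-unit difference.

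In the article's own terms (SD 6, one-sided 5%, 25 evaluable per arm), power is 90.3% unadjusted. It is 91.6% at a variance ratio of 0.95 and 95.0% at 0.80. The n needed for 90% power is 24 and 20.

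**Normality switch.** A simulation used 25 per arm, m = 28, s = 10, r from 0.3 to 0.7, two-sided 5%, and a Shapiro-Wilk test at 5% as the assumed criterion. The switched procedure had a type I error of 5.1 to 5.4%. The t and rank-sum decisions differed in about 2% of null trials and 6 to 7% of trials with a true effect.

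**The case against.** The strongest reply is that nothing here is an error. A comparison of mean change between randomised arms is unbiased over repeated randomisation, and chance imbalance is already covered by its nominal error rate. The trial was sized on the SD of ΔIMR itself, so design and analysis match. All of that stands. The exposure to imbalance is conditional on the allocation that actually occurs; it is not a bias of the method. It also stands that the gain may be nil: with an underlying SD of 10, correlations that match the article's SDs leave 0 to 2%.

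One could add that test details belong in a full protocol or SAP that is not shown. That covers the missing normality criterion. It does not cover the choice of test, which the article itself fixes as unadjusted and switchable.

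Three stronger readings are tempting and are not supported:

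- **A 35% gain.** The textbook ratio (1 + r)/2 gives 0.65 at r = 0.3. It ignores the entry cut at 25, and the article gives no basis for that correlation.
- **An invalid t test because the assumed SDs are 6 and 4.** A pooled test with 22 evaluable in the SD 6 arm and 29 in the other has a true two-sided size of 6.3%. With the split reversed it is 3.9%. The article does not say that the test is pooled. Even if it is, its size averaged over simple randomisation of 64 with 20% drop-out is about 5%.
- **Type I error inflated by the normality switch.** The simulation shows no material inflation.

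**Conclusion.** The point holds as an improvement to a valid analysis. The planned test uses no baseline information although that information exists for every participant, and the primary test and its estimand are not settled before the data are seen. The 0 to 20% lower variance rests on the assumed means, SDs and correlations and on equal underlying SDs at both times. It is an illustration that fits the article's ΔIMR SDs and not a bound. The case for adjustment does not depend on the upper end: at worst it costs about 1% of variance, and in the other rows it gains precision while removing the linear effect of chance baseline imbalance. The sample size stands.

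**What to change.** In section 2.9.3, name one primary analysis: ANCOVA of 12-month IMR on randomised group and baseline IMR, reporting the adjusted difference with its confidence interval. Using ΔIMR as the outcome on the same scale gives the same treatment effect, apart from sign if ΔIMR is defined as a reduction. Fix the scale, raw or log, now; the sample-size section is written on the raw scale. Keep the rank-sum test as a named sensitivity analysis only. Treat CFR and CTFC in the same way, each with its own baseline. Heteroscedasticity-robust standard errors are a reasonable addition given the assumed SDs of 6 and 4.

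The cost is a few sentences of analysis wording. No new measurement or extra participant is needed.
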